## Abstract

**Background:**

The phenomenon of restlessness, agitation, or cognitive disturbances experienced by dying patients is well-known in palliative care; more than half of these patients will experience delirium symptoms at end-of-life. When not identified early and effectively managed, delirium symptoms could lead to caregiver and patient distress and harm.

**Methods:**

Eighty patients with a prognosis of 7 days or less will be recruited for an open-label randomised control trial. The two arms compare oral-transmucosal haloperidol 2.5 mg vs olanzapine 5 mg over 72 h. The severity of agitation, delirium and toxicities of treatments will be compared at the 24th, 48th and 72nd hour after drug administration.

**Discussion:**

This trial is the first to compare anti-psychotics in the management of delirium at the dying stage in the home hospice setting using the oral transmucosal route. Ethical considerations, as well as recruitment procedures, are discussed.

**Trial registration:**

This study was registered in ClinicalTrials.gov – identifier NCT04750395

## Administrative information

Note: the numbers in curly brackets in this protocol refer to SPIRIT checklist item numbers. The order of the items has been modified to group similar items (see http://www.equator-network.org/reporting-guidelines/spirit-2013-statement-defining-standard-protocol-items-for-clinical-trials/).

## Introduction

### Background and rationale {6a}

Terminal delirium is a common syndrome in palliative care. It occurs within the final days of life in between 25 and 88% of dying patients and is perceived to be one of the most difficult end-of-life symptoms to manage [1]. In contrast to other types of delirium that are treatable (and hence reversible), terminal delirium is a complex and refractory syndrome that is often multi-factorial in aetiology. It is characterised by a diminished level of consciousness, an inability to focus or maintain attention, and a disturbance of cognition and perception (e.g. hallucination, agitation, and restlessness).

Delirium could have a profound impact on the well-being of the patients as well as the family caregivers. Family caregivers perceived a high level of stress both physically and psychologically in the management of delirious patients [2]. Similar distress was also observed by the investigators in the home-based hospice setting. Within community care, pharmacological therapies are utilised to manage the syndrome, the most commonly used being neuroleptics haloperidol and olanzapine.

Haloperidol is the first of the butyrophenone series of major antipsychotics. The mechanism of action of haloperidol for the treatment of psychotic disorders is unclear. However, its efficacy could be mediated through its activity as an antagonist of central dopamine type 2 receptors. Haloperidol also binds to alpha-1

adrenergic receptors, but with lower affinity, and displays minimal binding to muscarinic, cholinergic, and histaminergic (H_1_) receptors.

Olanzapine is a second-generation thienobenzodiazepine antipsychotic which displays potent antagonism of serotonin 5-HT2A and 5-HT2C, dopamine D1-4, histamine H1, and alpha1-adrenergic receptors. Olanzapine shows moderate antagonism of 5-HT3 and muscarinic M1-5 receptors, and weak binding to GABA-A, BZD, and beta-adrenergic receptors. Although the precise mechanism of action in schizophrenia and bipolar disorder is not known, the efficacy of olanzapine is thought to be mediated through combined antagonism of dopamine and serotonin type 2 receptor sites.

A recent Cochrane systematic review evaluating the effectiveness and safety of drug therapies to manage delirium symptoms in terminally ill adults has only found four clinical studies that included haloperidol and olanzapine, with high risks of bias and low to very low quality of evidence. Due to the absence of evidence from robust clinical trials, current recommendations are based on consensus or expert opinion, and clinical experience in the care of patients at the end of life [3]. Given these considerations, we believe there is immense value in comparing the therapeutic effects of haloperidol versus olanzapine within the hospice home care setting at the end of life; other researchers have encouraged this investigation to be pursued [4].

Hence, we propose an open-label randomised clinical trial to compare the effects of haloperidol and olanzapine in the management of terminal delirium in home hospice patients who are imminently dying. Key outcome measures are the reduction of delirium symptoms and the reduction of agitation. Secondary outcome is the adverse effect burden on patients.

### Objectives {7}

This study is a non-inferiority trial that aims to compare the effect of Oral Transmucosal (OT) haloperidol and olanzapine in the management of terminal delirium in dying patients receiving home hospice care. The study’s secondary objective is to record the frequency and severity of toxicity from treatment. It is hypothesised that OT Haloperidol will reduce the severity of agitation and of terminal delirium as effectively as OT olanzapine, i.e. Haloperidol will not perform “unacceptably worse” than olanzapine.

### Trial design {8}

A prospective, parallel, open-label, randomised controlled trial was designed. Informed consent will be obtained from the patient’s proxy at home. After obtaining consent, a primary caregiver at home (who may or may not be the proxy) will be identified to administer the trial medication and make observations as specified in the trial procedures. When a home hospice clinician identifies a patient, who meets the inclusion criteria, his or her proxy will be approached by the study team and invited to participate in the study. Patients will be randomly assigned to receive either OT haloperidol or OT olanzapine as treatment.

After commencement of the first dose of medication, each patient will be observed by their family caregiver and the attending clinician over 72 h (less if the patient dies earlier). Time-points for data collection will be at 24 h, 48 h, and 72 h after the first commencement of medication. Table 1 outlines the trial in the form of the SPIRIT figure.

**Table 1 Tab1:**
[figure not shown]
SPIRIT figure for clinical trial

This study defines “terminal delirium” as an episode of delirium that occurs during the dying phase, usually 72 h before death [5]. Episodes of delirium in the dying phase may be described as “terminal restlessness” or “terminal delirium”. The use of the label “terminal” implies a causal relationship between the dying phase and the delirium, although the aetiology is often multi-factorial. Given that the trajectory of death is often uncertain, patients who survive up to 7 days after their commencement in the trial will be included.

## Methods: participants, interventions, and outcomes

### Study setting {9}

The study will be conducted within HCA Hospice Care (HCA). HCA is the largest home hospice provider in Singapore, looking after more than 60% of patients living in the community with life-limiting conditions. The average length of service is three months. Patient census is around 900–1000 on any given day, supported by five teams of multi-disciplinary professionals across the island, including on-site 24/7 support.

### Eligibility criteria {10}

The Inclusion criteria for the trial are as follows:
Patient is above 21 years of age.Patient was diagnosed with a terminal illness and is receiving end-of-life care at home.Patient is assessed to be acutely dying (estimated prognosis of 3 days or less).Patient is diagnosed by the primary palliative care provider to have delirium, as described in the DSM-V [6]

The Exclusion criteria are as follows:
Patient does not have a caregiver at home.Patient has a prior history of dementia, psychosis, schizophrenia or any other mental health issue followed up by psychiatrists or other specialists.Patient is currently receiving or has been administered haloperidol or olanzapine less than a week before participating in the study.Patient has known allergies or adverse reactions to haloperidol or olanzapine.

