### Provisions for post-trial care {30}

As this trial involves patients whose prognoses are between 3 and 7 days, patient death is expected by the end of the trial. However, in the event the patient outlives the prognoses and survives, the patient’s primary nurse and staff will continue to provide standard palliative care to the patient. At this point, medical advice and end-of-life decisions will be made independently from the study. The patient’s survival (whether alive, discharged, or deceased) will be monitored up to day 7 of recruitment. If the patient is still alive after day 7, their data will be removed from the main analysis as they would no longer fall under the inclusion criteria of an imminently dying patient.

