### Sample size {14}

Based on validation studies by Breitbart et al. [13] and Lawlor et al. [14], the mean scores from the Memorial Delirium Assessment Scale for patients with delirium is roughly 18 (SD = 7.64). Jain et al. [10] reported that using either haloperidol or olanzapine led to a nearly 55% reduction in patients’ MDAS score (7–8 points). Based on this, we estimate 2 points to be the minimal important difference between haloperidol and olanzapine; a 2-point difference between the treatment arms is equivalent to a 25% difference in the reduction of a patient’s MDAS score. Table 3 details sample size calculations, using the parameters as presented above.

**Table 3 Tab3:** Sample size calculation for repeated measures design

Sample size calculation for repeated measures design	
Standard deviation (drawn from literature review)	7.64
Estimated minimal important difference (effect size)	2
Target power (1-β error probability)	.80
Target *alpha*	.05
Estimated required size per treatment arm	32
Estimated minimum sample size for two arms	64
Target recruitment size (accounting for 30% attrition)	80

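### The entry prognosis is stated in three incompatible ways, day-7 survivors are dropped for failing a criterion that does not exist, and the 30% attrition allowance fits neither a 3-day prognosis nor the target of 80

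*Protocol article*

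**What the plan says.** Three sections of the protocol article describe prognosis at entry:

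- Eligibility criteria {10}, the only eligibility list: "estimated prognosis of 3 days or less".
- Abstract, Methods: "Eighty patients with a prognosis of 7 days or less will be recruited".
- Provisions for post-trial care {30}: "this trial involves patients whose prognoses are between 3 and 7 days".

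Trial design {8}, in the text after Table 1, adds that because the course of dying is uncertain, "patients who survive up to 7 days after their commencement in the trial will be included".

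Two sections deal with patients who live longer. Provisions for post-trial care {30} states: "If the patient is still alive after day 7, their data will be removed from the main analysis". The reason given is that such patients no longer fall under the inclusion criteria. The closing paragraph of the adverse-event scale description, under Plans for assessment and collection of outcomes {18a}, gives the same reason but excludes them from the per-protocol analysis. The section on non-adherence and missing data {20c} says the analysis is by intention to treat.

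The last assessment is 72 h after the first dose. Table 3 under Sample size {14} requires 32 per arm, 64 in total, and sets a recruitment target of 80, described as allowing for 30% attrition.

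**The concern.** The wordings differ in substance. Three days or less and between 3 and 7 days meet only at 3 days, and 7 days or less covers both. A patient expected to live 5 days fails the inclusion criterion but fits the other two descriptions. A patient expected to live 1 day meets the inclusion criterion and the abstract but falls outside the post-trial care description.

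The entry prognosis bears on three things: to whom the result applies, how many patients can be assessed at 48 h and 72 h, and whether the attrition allowance is plausible.

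The day-7 rule adds a second problem. Eligibility is a clinician's estimate made before randomisation, and a patient correctly judged eligible does not become ineligible by living longer. Removing such patients conditions the analysis set on an outcome observed after randomisation, which intention to treat is meant to prevent.

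**Working it through.** **1. The stated target.** Inputs from Table 3: 64 required, 30% attrition, target 80. The base of 64 is taken as given here.

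- Usual inflation: 64 / (1 − 0.30) = 91.4, so 92.
- Simple mark-up: 64 × 1.30 = 83.2, so 84.
- Neither gives 80. The target is reproduced by 64 / (1 − 0.20) = 80, an allowance of 20%.
- At 30% attrition, 80 × 0.70 = 56 remain, 8 short of 64.

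**2. What 30% means beside a 3-day prognosis.** The final assessment falls at 72 h = 3 days. If losses by then are to stay within 30%, at least 70% of patients must be alive beyond the prognosis on which they were enrolled. This needs no survival model. It also implies a median survival above 3 days.

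**3. How far above 3 days.** The protocol gives no survival rate, so this part is an assumption. Take Weibull survival with median m and shape k, counting deaths only: S(t) = exp(−ln 2 × (t/m)^k). Setting S(3) = 0.70 gives (3/m)^k = 0.3567 / 0.6931 = 0.5146, so m = 3 / 0.5146^(1/k).

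| Shape k | Median needed (days) | Alive after day 7, 0.70^((7/3)^k) |
|---|---|---|
| 1 (constant hazard) | 5.8 | 44% |
| 2 | 4.2 | 14% |
| 3 | 3.7 | 1% |

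**4. Expected numbers at 72 h under constant hazard, deaths only.** S(3) = 0.5^(3/m).

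| Median (days) | Alive at 72 h | Of 80 |
|---|---|---|
| 1.5 | 25% | 20 |
| 3 | 50% | 40 |
| 5 | 66% | 53 |
| 7 | 74% | 59 |

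None of these rows reaches 64. Rescue use, reaching the daily dose limit, intolerable toxicity, withdrawal and hospital admission also end participation {11b} and would lower the numbers further.

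**5. The day-7 rule applied as well.** Under constant hazard, the share alive at 72 h and dead by day 7 is S(3) − S(7) = x − x^(7/3), with x = S(3). It is largest at x = (3/7)^(3/4) = 0.53, where it equals 0.53 − 0.23 = 0.30. In that model at most about 30% of patients would have a 72-h assessment and stay in the main analysis, whichever entry prognosis is used. With a rising hazard the loss is smaller, as the last column of the first table shows.

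**6. The day-7 rationale against the criteria.** The inclusion list in {10} covers age, terminal illness with end-of-life care at home, estimated prognosis and a delirium diagnosis. Observed survival is not on it. The survival window in {8} is a rule about who is kept after entry, and the two sections that apply the exclusion name different analysis sets (main and per-protocol).

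**The case against.** The best defence is that the article has a two-part rule: a 3-day clinical estimate at entry, and a 7-day window of actual survival that allows for imprecise estimates. On that reading the abstract and the post-trial care section are loose paraphrases, and recruiting staff would apply the eligibility list. Much of this stands. A reader might infer that different populations will in fact be enrolled; the documents show only that the population is described inconsistently. But the window concerns survival after entry, while the abstract and the post-trial care section both speak of prognosis, so it explains where the 7 may come from without making the three statements agree.

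A second tempting inference is that median survival must reach 5.8 days for the allowance to hold. That figure belongs to constant hazard alone, which is questionable in imminently dying patients; a rising hazard brings it down to 4.2 or 3.7 days. Nor do the documents show that the 30% allowance will fail. Clinicians' estimates are imprecise, attrition is not defined as death before 72 h, and data up to discontinuation are kept, so a death at 60 h still leaves 24-h and 48-h scores.

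A reader might also take the statement "As this trial involves patients whose prognoses are between 3 and 7 days, patient death is expected by the end of the trial" as expecting death by 72 h. The end of the trial there could equally mean day 7, so nothing here rests on it.

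Finally, settling the prognosis would not by itself cure the attrition problem. The mismatch between 30% and 80 and the day-7 exclusion are separate faults and need their own corrections.

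**Conclusion.** The inconsistency in entry prognosis stands on the text alone. So does the fault in the day-7 rationale: it appeals to a criterion that the inclusion list does not contain, and it removes randomised patients from a main analysis declared to be intention-to-treat.

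The arithmetic fault is also certain: 80 covers 20% attrition on 64, not 30%. The shortfall is 8 completers at 30% attrition, or 12 recruits against the 92 needed.

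The tension between 30% attrition and a 3-day prognosis is firm in direction but uncertain in size. At least 70% of patients would have to outlive the prognosis, and the median this needs is about 3.7 to 5.8 days, assuming Weibull shapes from 3 down to 1 and deaths only. It makes the allowance hard to justify as written, but does not show that it will be missed. The point should be corrected, and most of the correction is wording.

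**What to change.** 1. State one entry prognosis, judged by the clinician at enrolment, in the same words in the abstract, Eligibility criteria {10} and Provisions for post-trial care {30}. Which prognosis it should be is for the investigators; this review does not say. Describe the 7-day window in Trial design {8} as observed survival, separate from eligibility.
2. In Provisions for post-trial care {30} and in the matching paragraph under {18a}, delete the statement that day-7 survivors no longer meet the inclusion criteria. Keep all such randomised patients in the intention-to-treat main analysis, and make any exclusion of day-7 survivors a sensitivity analysis only.
3. In Sample size {14}, restate the attrition allowance and the expected number assessed at 72 h under the chosen criterion, with the survival assumption given. Correct the mismatch: either the allowance behind 80 is 20%, or a 30% allowance on 64 needs 92.

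The cost is protocol wording, one added sensitivity analysis, and a stated attrition figure or recruitment target that will look less favourable.

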### Outcomes {12}

The primary outcome is the reduction in delirium severity as measured with the Memorial Delirium Assessment Scale (MDAS). Secondary outcomes are the reduction in the severity of agitation as measured with the Richmond Agitation-Sedation Scale modified for palliative care (RASS), and the frequency and severity of medication toxicities, as measured using the National Cancer Institute Common Terminology Criteria for Adverse Events (NCI-CTCAE). These data will be collected over four time-points: (i) baseline, (ii) 24 h after commencement, (iii) 48 h after commencement, and (iv) 72 h after commencement.

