#### The Richmond Agitation-Sedation Scale modified for palliative care

The RASS is a simple observational instrument assessing levels of sedation and agitation. It requires no patient input and ranges from + 4 (overly combative) to − 5 (unarousable). It is considered less time-consuming and easier to use than other similar instruments [15]. Developed for adult intensive care unit patients, the scale demonstrated strong inter-rater reliability in that setting. A modified version was designed for use in the palliative care setting, which produced acceptable psychometric properties. Hui, et al. had caregivers using the RASS to assess patients, which gave ratings similar to clinicians [16]. As part of scoring calibration with the caregivers, the attending study team members will guide the caregivers to provide the first score during the time of the first dose. Subsequently, caregivers will chart the patient’s agitation using the RASS every 6 h after the first dose. If breakthrough medication is required, the caregiver will also chart the time of administration and provide a RASS score.

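### The agitation outcome uses raw RASS change in patients who need not be agitated, so it mixes less agitation with deeper sedation

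*Protocol article*

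**What the plan says.** **Who enters.** Protocol article, Eligibility criteria {10}, requires that "Patient is diagnosed by the primary palliative care provider to have delirium, as described in the DSM-V". The other inclusion criteria concern age, terminal illness with care at home, and prognosis. None of the inclusion or exclusion criteria refers to agitation. Background and rationale {6a} says of terminal delirium: "It is characterised by a diminished level of consciousness, an inability to focus or maintain attention". Agitation appears there only as one example of disturbed cognition and perception.

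**What is claimed.** The same section states: "Key outcome measures are the reduction of delirium symptoms and the reduction of agitation". Objectives {7} describes a non-inferiority trial and adds: "It is hypothesised that OT Haloperidol will reduce the severity of agitation and of terminal delirium as effectively as OT olanzapine". Outcomes {12} makes MDAS delirium severity primary and reduction in agitation on the RASS secondary.

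**How agitation is measured and analysed.** The section on the scale says: "The RASS is a simple observational instrument assessing levels of sedation and agitation". It gives the range as +4 to −5. Caregivers score every 6 hours and at breakthrough doses, and give the first score at the first dose with guidance from the study team. Statistical methods {20a} applies repeated-measures ANOVA to the RASS scores with no condition on baseline. The section on non-adherence and missing data {20c} makes the analysis intention-to-treat, and additional analyses {20b} are marked as not applicable.

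**The concern.** The population, the scale and the analysis rule do not together measure the stated agitation objective. A patient at RASS 0 or below at baseline meets the entry criteria but cannot show a reduction in agitation from baseline. On the raw score, that patient's improvement (waking) is a rise and deterioration (deeper sedation) is a fall. An agitated patient's improvement is also a fall. The arm mean adds these together.

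The section on the NCI-CTCAE names over-sedation as a possible side effect of either drug. Under the stated rule, that toxicity is credited to the drug as reduced agitation. A reader of the results could not tell whether a fall in mean RASS reflects settled patients or sedated ones, nor whether similar arm means reflect similar control of agitation.

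**Working it through.** The document has no RASS sample size, standard deviation, margin or share of non-agitated patients, so there is no planned figure to reproduce. The 32 per arm in the sample size table was derived for the MDAS and is borrowed below only as an arm size. All other inputs in steps 2 to 4 are assumptions.

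**1. What the raw score counts.** Some possible patient courses, scored raw and one-sidedly (values below 0 set to 0):

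| Course | Raw change | One-sided change |
|---|---|---|
| +2 to 0 (settles) | −2 | −2 |
| −2 to 0 (wakes) | +2 | 0 |
| −1 to −4 (deeper sedation) | −3 | 0 |
| +2 to −4 (settles, then over-sedated) | −6 | −2 |
| 0 to +2 (becomes agitated) | +2 | +2 |

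On the raw score, the patient who becomes more sedated shows a larger agitation reduction than the patient who settles. If half the patients go from +2 to 0 and half from −2 to 0, the raw mean change is 0.5 × (−2) + 0.5 × (+2) = 0, although every patient improved.

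**2. Effect on the arm difference.** Let h be the share with baseline RASS of 0 or below, d the difference in mean change (haloperidol minus olanzapine) among agitated patients, and s the same difference among the rest. The observed difference is

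D = (1 − h)d + h·s.

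- Dilution (s = 0): D = 0.7d, 0.5d and 0.3d for h = 0.3, 0.5 and 0.7.
- Spurious separation (h = 0.5, d = 0, s = −1): D = −0.5, with no difference in control of agitation.
- Masking (h = 0.5, d = −1, s = +1): D = 0, with a real difference.

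The direction therefore depends on s, which the document does not give.

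**3. Power under dilution alone.** Assume d = 0.7 SD in size, s = 0, constant SD, two-sided 0.05, noncentral t, and 32 per arm in total, so that a subset agitated at baseline has 32(1 − h) per arm.

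| h | All patients, difference 0.7(1 − h) SD | Baseline-agitated subset, difference 0.7 SD |
|---|---|---|
| 0.3 | 0.49 | 0.63 |
| 0.5 | 0.28 | 0.48 |
| 0.7 | 0.13 | 0.31 |

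At h = 0 the power is 0.79. Under this assumption the subset loses patients but gains power over the all-patient comparison.

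**4. Non-inferiority under dilution alone.** Suppose a margin M = 0.5 SD, and haloperidol truly worse by exactly M among agitated patients. With SE = √(2/32) = 0.25 SD, the chance of declaring non-inferiority at one-sided 0.025 is Φ(hM/SE − 1.96):

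- h = 0: Φ(−1.96) = 0.025
- h = 0.3: Φ(0.6 − 1.96) = 0.087
- h = 0.5: Φ(1.0 − 1.96) = 0.169
- h = 0.7: Φ(1.4 − 1.96) = 0.288

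These values judge the all-patient result against the effect in agitated patients.

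**The case against.** **Broad entry is legitimate, and agitation is secondary.** This stands. The MDAS matches an entry criterion based on delirium, and no eligibility change is needed.

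**A reader might infer that the arms are necessarily pulled together, so that the hoped-for non-inferiority conclusion is favoured.** The document does not support that. Dilution requires s = 0, and differential sedation could equally separate the arms. No RASS margin is stated, and the planned ANOVA tests for a difference; reading a non-significant result as equal efficacy would be a separate error. Under pure dilution, (1 − h)d is also the true mean effect in the enrolled population. It misleads only as a statement about agitated patients.

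**A reader might infer that calm patients carry no information and should be dropped.** They can become agitated later, and 6-hourly charting would show it. Replacing the all-patient analysis with a baseline subset would also depart from intention-to-treat. As the article describes it, the first RASS is a caregiver rating made after randomisation in an open-label trial, so the subset could depend on known treatment. Nor would the subset alone cure the course from +2 to −4.

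**The share of non-agitated patients may be small.** The article also uses the label of terminal restlessness and ties rescue partly to uncontrolled agitation, so referrals may be mostly agitated patients. That is possible, but no criterion ensures it.

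**RASS detail may sit in an analysis plan not shown.** Further detail may. But the article itself fixes the scale, the model and the population, and those as stated do not isolate agitation.

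**Conclusion.** The concern holds for the secondary agitation outcome only. As written, raw RASS change in all randomised patients does not measure reduction of agitation: it mixes agitation with sedation, lets opposite improvements cancel, and credits over-sedation as benefit. That conclusion rests on the stated entry criteria, scale and analysis rule, and needs no assumed figure.

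Direction and size are not established. The figures in steps 2 to 4 are illustrations over an assumed h of 30% to 70%, with an assumed effect and margin. If nearly all referred patients are agitated at baseline, the dilution part is small; over-sedation of agitated patients would still be counted as benefit. The point is worth correcting because the data needed are already collected.

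**What to change.** In Outcomes {12} and Statistical methods {20a}:

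1. Score agitation one-sidedly, with RASS values below 0 set to 0, and analyse it in all randomised patients.
2. Report RASS values below 0 separately, by arm, as sedation.
3. Prespecify the comparison of agitation reduction in patients with baseline RASS of +1 or higher, alongside the all-patient analysis and not in place of it. One-sided scoring stops sedation from counting as benefit, but calm patients still enter at 0; the subset addresses that.
4. Record the baseline RASS before the allocation is disclosed to the caregiver, so that membership of the subset does not depend on known treatment.

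The MDAS analysis and the eligibility criteria stay as they are. The cost is slightly more analysis work, a change in the order of steps at the first visit, and a smaller, less precise subset: at h = 0.5, about 16 per arm (32 of the 64 planned), before further loss to death.
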